### Primary outcome measure

Roland Disability Questionnaire for Sciatica (RDQ) is an illness-specific 23-item functional assessment questionnaire that is frequently used for low back pain and sciatica [8-11]. The score, ranging from 0 to 23, reflect a sum of items experienced by the patient. The higher the score the more disabling the sciatica is perceived. The score will be analyzed as a continuous outcome variable. For descriptive purposes, "Recovery" (at the individual level) is defined by a difference of at least 11 points from baseline. A difference of 4 points for the averages between the two randomization arms is considered the maximum for "equivalence" of the two treatment modalities. The RDQ has established validity, reliability and responsiveness to change [12]. This outcome measure is used to determine the power of the study.

Other parameters that will be used from primary endpoint analyses are:

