When analyzing the primary outcome measure, Roland, the primary analysis will be a repeated measurement analysis of variance, hence estimating the original measurements. As a secondary analysis of this primary outcome variable, we will define "Roland-recovery" as a change of at least 11 points between baseline and any point in time post randomization. This dichotomization of the Roland score will be used as the outcome variable in a Cox regression analysis modeling time till recovery. The multivariate analysis will be performed along the same principles for variable selection and model building as outlined above.

A subgroup analysis is preplanned and will be performed to assess differences in treatment effect in subgroups of patients. (Table 4)

**Table 4 T4:** Prognostic variables in subgroup analysis

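### The secondary Cox analysis defines recovery as an 11-point RDQ change, which a patient entering at 10 or less cannot reach even at a score of 0

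*Protocol article*

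**What the plan says.** Primary outcome measure (protocol article) gives the scale: "The score, ranging from 0 to 23, reflect a sum of items experienced by the patient", and "The higher the score the more disabling the sciatica is perceived". The same section says that individual recovery "is defined by a difference of at least 11 points from baseline", and labels this as descriptive.

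Statistical analysis then gives the cut-off an inferential role. For the RDQ, "the primary analysis will be a repeated measurement analysis of variance" on the scores themselves. As a secondary analysis, Roland-recovery is defined "as a change of at least 11 points between baseline and any point in time post randomization", and "This dichotomization of the Roland score will be used as the outcome variable in a Cox regression analysis modeling time till recovery".

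Three other places matter:

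- Table 1 asks for radicular pain of a minimum duration, an operation indication and a herniation confirmed on MRI. It sets no lower limit on the RDQ.
- Statistical analysis keeps all patients in their randomized groups.
- No section offers an absolute score or a percentage change as an alternative event, or states how patients with low baseline scores enter the Cox model.

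**The concern.** A time-to-event model needs an event that everyone in the risk set could have. Here the event is a fixed fall on a scale with a floor at 0, so whether it is possible depends on the entry score. A patient who enters at 10 and reaches 0 has the best result the questionnaire can record, yet is counted as not recovered throughout.

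These patients are not censored early. They remain in the risk sets of both arms until follow-up ends. Two things follow. The proportion recovered in each arm is capped below 100%, and any difference between arms in that proportion shrinks by the same factor. The hazard ratio no longer describes the patients who can recover, and moves towards 1. What is at stake is the accuracy of the reported recovery proportions and of the hazard ratio for time to recovery.

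**Working it through.** **1. The plan's own figure.** The document gives no figure for the Cox analysis. Its one computed figure is the sample size, checked here because 110 is used as the denominator below. Inputs from Sample size: margin 4, assumed difference 1, SD 5, alpha 0.05 (taken as one-sided), power 0.90.

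- Normal approximation per arm: 2 × [5 × (1.645 + 1.282) / (4 − 1)]² = 47.6, so 48.
- The t-distribution version has power 0.899 at 48 and 0.904 at 49 per arm. This gives 49 per arm, 98 in total, as stated.
- Loss of 8%: 98 / 0.92 = 106.5, so 107. The planned 110 covers this.

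This calculation rests on mean RDQ and does not involve the recovery definition.

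**2. Who can have the event.** Recovery is read as a fall, since higher scores are worse. The text says only change, but counting an 11-point worsening as recovery would make no sense. The largest possible fall is baseline − 0.

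| Baseline RDQ | Largest fall | Score needed for the event |
|---|---|---|
| 0 to 10 | 0 to 10 | none, the event is impossible |
| 11 | 11 | 0 |
| 12 | 12 | 0 or 1 |
| 23 | 23 | 12 or less |

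Of the 24 possible scores, 11 (0 to 10) rule the event out.

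**3. How many patients (assumed).** The document gives no baseline mean or SD. The calculation uses a normal distribution rounded to whole scores and truncated to 0–23, where Φ is the standard normal distribution function:

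P(baseline ≤ 10) = [Φ((10.5 − m)/s) − Φ((−0.5 − m)/s)] / [Φ((23.5 − m)/s) − Φ((−0.5 − m)/s)]

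| Assumed SD | mean 14 | mean 16 | mean 18 |
|---|---|---|---|
| 3 | 12.2% (13.4 of 110) | 3.4% (3.7) | 0.6% (0.7) |
| 4 | 19.2% (21.2) | 8.7% (9.6) | 3.3% (3.7) |
| 5 | 24.8% (27.2) | 14.5% (15.9) | 7.7% (8.5) |

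The range is about 1% to 25%, or roughly 1 to 27 of 110 patients.

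**4. Effect on the hazard ratio (assumed).** Let π be the share who can never have the event, equal in both arms. Among the rest, times to recovery are taken as exponential with a true hazard ratio of 1.50 and 52 weeks of follow-up. In arm k the proportion still unrecovered is S_k(t) = π + (1 − π)exp(−λ_k t), and the event density is f_k(t) = (1 − π)λ_k exp(−λ_k t). Here λ_0 = ln 2 / median in the slower arm, and λ_1 = 1.5 λ_0. The unadjusted Cox estimate tends to exp(b), where b solves

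∫ [f_1 − (f_0 + f_1) · S_1 e^b / (S_0 + S_1 e^b)] dt = 0 over 0 to 52 weeks.

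| Median in slower arm | π = 5% | π = 10% | π = 20% |
|---|---|---|---|
| 8 weeks | 1.33 | 1.27 | 1.19 |
| 26 weeks | 1.45 | 1.41 | 1.36 |

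A simulation with a rate of 0.05 per week (median ln 2 / 0.05 = 13.9 weeks) gave about 1.33 at 10% and 1.24 at 20%. The size depends on the assumed speed of recovery. The direction was towards 1 in every case.

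**5. Recovery proportions.** The observed proportion in each arm is (1 − π) times the proportion among patients who can recover. With π = 10%, both proportions and their difference are multiplied by 0.90.

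**6. What stratifying does.** In a Cox model stratified at baseline 10 or less versus 11 or more, the lower stratum has no events and adds nothing to the partial likelihood. The estimated hazard ratio is therefore the same as in a model restricted to baseline 11 or more. Because baseline RDQ is recorded before randomization, that comparison remains a randomized one.

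**The case against.** The strongest reply is that little depends on this analysis. It is labelled secondary, and the 11-point cut-off is introduced as descriptive. This stands, and it limits the weight of the point. It does not remove it, because the article itself fixes both the event and the model. This is not a detail left to a fuller plan.

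Second, an operation indication and persistent radicular pain make low RDQ scores less common. This also stands, and the true share may be near the lower end of the range. Neither criterion is expressed as an RDQ value, so low scores are not excluded.

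Third, the plan allows baseline covariates in its models and applies the same principles to the Cox model. This helps in part. In a simulation with a true hazard ratio of 1.50 and baseline mean 16, SD 5 (assumed), the estimate was about 1.28 unadjusted, about 1.39 with baseline RDQ as a linear covariate, and about 1.50 when stratified at 10 or less. Adjustment is optional in the text, and a linear term does not fully repair the problem.

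A reader might go further and infer that a hazard ratio pulled towards 1 helps the trial claim non-inferiority. The documents do not support that. Equivalence is judged on a 4-point difference in mean RDQ, the Cox model has no margin, and no section ties the non-inferiority conclusion to it. A reader might also take the Cox model as the trial's only test of the trade-off in speed of recovery described in Background. That does not hold either. The RDQ is compared at 8 weeks as well as at 1 year, and perceived recovery on a Likert scale, which has no link to the RDQ floor, is collected at every time point in Table 3.

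**Conclusion.** The definition is wrong as written, for the secondary time-to-recovery analysis only. That the event is impossible from a baseline of 10 or less follows from the document's own scale and threshold, and needs no assumption beyond reading recovery as a fall.

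The size does rest on assumptions. The affected share is unknown, and the 1% to 25% range comes from assumed baseline distributions. The attenuation, from 1.50 to about 1.27–1.41 at a 10% share, also assumes exponential recovery times, an equal share in both arms and no adjustment for baseline. If almost every patient entered at 11 or more, the practical effect would be small.

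The primary analysis, the margin and the sample size of 98 (110 with losses) stand as they are.

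**What to change.** In Statistical analysis, after the definition of Roland-recovery, add one of the following:

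- **Keep the 11-point event.** Fit the Cox model stratified by baseline RDQ (10 or less versus 11 or more), or restrict it to patients with baseline RDQ of 11 or more. Report the number of patients below 11 in each arm, and give the recovery proportions for patients at 11 or more.
- **Change the event.** Define one that every patient can reach, for example an absolute low RDQ score or a percentage fall from baseline. Keep the 11-point rule as a sensitivity analysis. This option needs care. Under a plain 50% rule a fall from 2 to 1 would count, well below the 4 points that the protocol takes as the minimum important difference. An absolute score needs a rule for patients already at or below it on entry.

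The first option is the simpler correction. It costs a sentence of text and one model specification, and uses baseline RDQ scores that are already collected. Its downside is that the restricted analysis no longer covers every randomized patient, but those left out can contribute no event.

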## Background

In the majority of patients, experiencing their first episode of sciatica due to lumbar disc herniation, the symptoms recede to a non-disabling level within a period of six weeks [1]. The historical mainstay in the treatment of sciatica in patients in which the complaints are refractory to conservative treatment is discectomy [2]. This treatment is aimed at the removal of the herniated disc fragment that is the cause of nerve root compression. Another way of decompressing the nerve root is by inducing a negative pressure in the intervertebral disc by removal of tissue. Several percutaneous techniques are based on this principle [3]. Percutaneous Laser Disc Decompression (PLDD), being one of these techniques, is a modality in which laser energy is delivered to the nucleus pulposus by means of a fiber [4]. This fiber is inserted through a thin needle via a posterolateral percutaneous approach under local anesthesia. The absorption of the applied laser energy leads to vaporization of the water content of the nucleus pulposus in combination with a change in protein structure thereof. The subsequent volume reduction causes a disproportionate decrease in intradiscal pressure and relieves the nerve root. The first clinical percutaneous laser disc decompression was performed in Europe by Choy and Ascher in 1986 [5]. The U.S. Food and Drug Administration approved PLDD for use in the USA in 1991.

PLDD is an attractive treatment because of the minimally invasive nature and therefore the assumed decrease in risk of structural damage to the muscles, bone, ligaments and nerves. Furthermore, the patients are expected to have less back pain, shorter hospitalization and a shorter reconvalescence period than with conventional surgery. The actual recovery of the sciatica however, might take more time than after conventional surgery, although immediate resolution of the symptoms does occur.

Although several cohort studies have been published, and FDA approval was given, to date no randomized trial has been performed comparing PLDD with conventional surgical procedures. The cohort studies showed the safety and potential benefits of PLDD. No evidence regarding the efficacy and cost-effectiveness of PLDD, compared to conventional surgery, is available to date [6].

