Currently, there is broad consensus that conventional surgery is the gold standard for surgical intervention for sciatica; therefore PLDD has to be compared to conventional surgery in order to assess the cost-effectiveness. The result will be a trade-off between the expected more swift recovery of the patients in the 'gold standard' group versus the minimally invasive nature, lower costs and patient comfort of the PLDD treatment, which might take a slightly longer period to full recovery. Several subgroups will be identified in a post-hoc analysis, using pre-defined potential risk factors, which might especially benefit from the PLDD treatment. It is hypothesized that the potential result, immediately after treatment, is non-inferior at longer follow-up. In this study the patients will therefore be assessed for primary endpoints at 8 weeks and 1-year follow up and additional endpoints up to 2 years.

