### Outcome assessment

The assessment of outcome will use several validated outcome parameters as described below. Patients will undergo neurological examination by the research nurse at 4, 8, 26, and 52 weeks (Table 2). Questionnaires will also be filled out at these follow-up moments. At 1, 2, 6, 12, 38, 78, and 104 weeks the questionnaires will be filled out by the patient at home, and subsequently send to the data collection center by regular mail. Outpatient control by the neurosurgeon takes place at 8 weeks and thereafter if deemed necessary. The follow-up moments of data collection and outcome measures are listed in Table 3.

**Table 2 T2:** Neurological examination

*Straight leg raising test (Lasègue)
*Crossed straight leg raising test (Crossed Lasègue)
*Sensory loss
*Dermatome anesthesia
*Muscle weakness
*Knee tendon reflex difference
*Ankle tendon reflex difference
*Finger-ground distance in centimeter

Lasègue's sign is defined positive if the patient experiences a typically dermatomal area of pain reproduction and pelvic muscle resistance below a unilateral 60 degrees angle provocative straight leg raising. 'Crossed positive' if the same experience was noted with straight raising of the contralateral leg below 90 degrees.

**Table 3 T3:** Data collection and outcome measures

	RN			RN		RN		RN		RN		
**Time in weeks**	***X***	0	2	***4***	6	***8***	12	***26***	38	***52***	78	104

Treatment preference patient	v	v								v		v

Neurological examination	v			v		v		v		v		

Likert	v	v	v	v	v	v	v	v	v	v	v	v

Prolo	v			v		v		v		v		

Severity of complaints (VAS)	v	v	v	v	v	v	v	v	v	v	v	v

Functional status (Roland DQS)	v	v	v	v	v	v	v	v	v	v		v

McGill	v									v		v

Health status (Rand/SF 36)	v			v		v		v		v	v	v

EuroQol	v	v	v	v	v	v	v	v	v	v	v	v

SFB Index	v			v		v		V		v		

Costs (diary)	v		v	v		v	v	V	v	v		

Surgery/PLDD		v										

Complications		v		v		v		v		v		

"RN" marks the scheduled meetings with the Research Nurse.

Our goal is to show clinical equivalence between the two treatment strategies at various time points. The 1-year follow-up will be the most important clinical landmark. The cost-effectiveness analysis will therefore be performed using the clinical and economical parameters at 1 year.

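### The Cox analysis of time to Roland recovery points to one overall hazard ratio, although the protocol's own expectation (surgery faster early, PLDD non-inferior later) makes proportional hazards doubtful

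*Protocol article*

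**What the plan says.** The section Statistical analysis makes the continuous Roland score primary: "the primary analysis will be a repeated measurement analysis of variance". As a secondary analysis of that outcome, "we will define 'Roland-recovery' as a change of at least 11 points between baseline and any point in time post randomization", and then "This dichotomization of the Roland score will be used as the outcome variable in a Cox regression analysis modeling time till recovery".

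The Cox model is to be built on the same principles as the other models in that section. These provide for interactions between treatment and the stratification factors or main baseline covariates. The treatment effect is reported as an overall adjusted value, broken down only where one of those interactions is significant, and inference comes from the most reduced model that still fits and still yields a treatment effect. Time since randomization is not named as a modifier of the effect.

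The Background describes the expected course. On PLDD: "The actual recovery of the sciatica however, might take more time than after conventional surgery". The trade-off to be studied sets the "expected more swift recovery of the patients in the" gold-standard (surgical) group against the lower burden and cost of PLDD, "which might take a slightly longer period to full recovery". The hypothesis is that the PLDD result "is non-inferior at longer follow-up".

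In Table 3 (Outcome assessment), the row starting "Functional status (Roland DQS" is ticked at weeks 0, 2, 4, 6, 8, 12, 26, 38, 52 and 104.

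**The concern.** A Cox model with one treatment term summarises the whole follow-up by a ratio taken to be constant. That suits a treatment that is slower, or faster, by the same factor throughout. The Background describes something else: a delay early on and a result that is acceptably close later. If that course occurs, the fitted ratio is a weighted average of different effects, and the weights depend on when recoveries happen and when follow-up stops.

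The section Statistical analysis lists differences in time to recovery beside differences in outcome measurements as what the analysis will assess, and the Background frames the trial as a trade-off that includes speed of recovery. A reader will want two answers: how much later PLDD patients recover, and whether the arms are level at 1 year, which the article ranks as the leading clinical time point. A single averaged ratio can understate the early delay and also suggest a lasting deficit when none remains at 1 year.

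**Working it through.** **Figures in the article.** It states no event count, recovery rate, hazard ratio or power for the Cox analysis, so there is no figure of that kind to reproduce. The stated sample size (98, or 49 per arm) concerns the mean Roland score. With margin 4, assumed difference 1, SD 5, one-sided alpha 0.05 and power 0.90, n per arm = 2 × (1.645 + 1.282)² × 5² / (4 − 1)² = 47.6, so 48; the t-based version gives 49. The figure reproduces, and it does not depend on the recovery analysis.

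**Assumed curves.** These are an illustration of convergence by 1 year, not figures from the article. Hazard ratios are PLDD versus surgery, so a value below 1 means slower recovery after PLDD. With S the proportion not yet recovered, the ratio in an interval is ln(S_end/S_start) for PLDD divided by the same quantity for surgery.

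| Weeks | Surgery recovered by end | PLDD recovered by end | Interval ratio |
|---|---|---|---|
| 0–2 | 25% | 10% | 0.37 |
| 2–4 | 40% | 18% | 0.42 |
| 4–8 | 55% | 32% | 0.65 |
| 8–12 | 60% | 42% | 1.35 |
| 12–26 | 66% | 60% | 2.29 |
| 26–52 | 70% | 70% | 2.30 |
| 52–104 | 72% | 72% | 1.00 |

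Example, weeks 0–2: ln(0.90)/ln(0.75) = 0.105/0.288 = 0.37.

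**What one Cox term reports.** Fitted to a large simulated sample (8,000 per arm) from these curves, the ratio is 0.49 with follow-up to week 8, 0.73 to week 26, 0.82 to week 52 and 0.83 to week 104. Only the length of follow-up differs. As a control, with a true constant ratio of 0.6 the fitted value stays at 0.59 to 0.60 at every horizon.

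**What proportionality would impose.** From the week-8 figures, the constant ratio is ln(0.68)/ln(0.45) = 0.386/0.799 = 0.483. With surgery at 70% by week 52, PLDD would be held to 1 − 0.30^0.483 = 44%. A constant ratio of this size allows near-convergence only if almost everyone recovers. The event needs an 11-point change on a 0–23 scale and Table 1 sets no minimum baseline score, so near-universal recovery cannot be taken for granted.

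**What the alternative summaries report on the same curves.** Recovered at week 8: 55% versus 32%, a difference of 23 points. At week 52: 70% versus 70%, a difference of 0. Restricted mean time to recovery to week 52 is the area under the unrecovered curve (straight lines between time points):

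- Surgery: 1.75 + 1.35 + 2.10 + 1.70 + 5.18 + 8.32 = 20.4 weeks
- PLDD: 1.90 + 1.72 + 3.00 + 2.52 + 6.86 + 9.10 = 25.1 weeks
- Difference: 4.7 weeks

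These figures separate the early delay from the 1-year result.

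**Visit spacing.** The gaps between Roland assessments after week 0 are 2, 2, 2, 2, 4, 14, 12, 14 and 52 weeks. With recovery dated to the next visit, the week-52 ratio is 0.821 with Efron ties and 0.830 with Breslow ties, against 0.820 with exact times. At week 8 the values are 0.486, 0.514 and 0.486. The largest shift is about 0.03.

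**The case against.** The strongest reply is that the article does not predict non-proportional hazards. Non-inferiority is not equality: the margin is 4 points on the mean score, and nothing says that the proportions with an 11-point change become equal. A constant ratio can also narrow the gap. At 0.75, surgery going from 60% to 95% recovered takes PLDD from 1 − 0.40^0.75 = 50% to 1 − 0.05^0.75 = 89%, so the gap falls from 10 to 6 points with exactly proportional hazards. The wording on PLDD is hedged, and the Background adds that immediate relief does occur.

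The planning difference of 1 point also implies something milder than the curves above. With SD 5 and a rough normal approximation, surgery at 60% and 80% recovered at weeks 8 and 52 would go with PLDD at about 52% and 74%. The cumulative hazard ratios are ln(0.48)/ln(0.40) = 0.80 and ln(0.26)/ln(0.20) = 0.84, which is close to proportional.

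This stands. A reader might infer that the ratio must later exceed 1; the article does not support that, and the values above 1 in the table come from assuming equal proportions at week 52. What remains is that an effect changing over time is foreseeable from the stated expectation, and the planned summary is a good one only if it does not occur.

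It is also fair that the article never says a single hazard ratio will be reported, and that proportional-hazards checks and tie handling commonly sit in an analysis plan not shown here. Their absence is not the complaint. The one overall ratio is a reading of the model-building rules the article does state.

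A reader might further infer that recovery is observed too sparsely for a Cox model. It is not: the Roland score is taken every 2 weeks to week 8, both arms share the schedule, and the numerical effect is small.

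**Conclusion.** The point holds in a limited form. Under the stated modelling rules, the Cox analysis leads to one overall treatment hazard ratio, and the Background gives reason to doubt that the ratio is constant. If the arms converge by 1 year, that ratio depends on follow-up length (about 0.49 to week 8 against 0.82 to week 52 under the assumed curves) and answers neither the early nor the 1-year question clearly. If the true difference is small and steady, as the planning figure would suggest, the ratio is nearly constant and little is lost. The size therefore rests on assumed recovery curves; from the article comes only the reason to expect an effect that changes over time.

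The consequence is confined to a secondary analysis. One might infer that the non-inferiority conclusion is at risk, but it rests on the repeated-measures analysis of the Roland score, and neither that analysis nor the sample size uses the recovery event. The change is worth making because it is cheap and removes the dependence on an assumption that the protocol itself puts in doubt.

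**What to change.** Keep the Cox model as a supportive analysis. For this secondary analysis, prespecify by arm the proportion who have reached Roland-recovery by week 8 and by week 52, and the difference between arms in restricted mean time to recovery to week 52, each with a confidence interval. State that the conclusion on time to recovery is drawn from these figures, so that it does not rest on proportional hazards.

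Replacing Cox outright with a discrete-time model split into early and late periods is not needed. With about 50 patients per arm the late-period estimate would rest on few events, so that trade-off is open to debate.

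No new data are required, since the Roland score is already scheduled at both time points. The cost is a few lines of analysis-plan wording, slightly more programming, and two or three reported numbers in place of one hazard ratio.
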